### 3.4 Presenting IEM frequencies in the child population

The frequency of inborn errors of metabolism detected using tandem mass spectrometry, depending on the geographical location and type of IEM in western Kazakhstan during the period from 2023 to 2024, can be represented graphically in the form of accumulation diagrams demonstrating the contribution of AAD, OA, and FAOD to the total incidence of IEM. Also, these data can be presented in the form of a table. The data will include the total number of IEM cases in the high-risk group of children and the absolute number and frequency of cases for each identified disease. Detection rates for selective screening and incidence will be calculated according to the number of children born in western Kazakhstan during the study period, in 2023–2024, for each specific disease. These data will allow for estimating the number of affected male and female children and determining which IEMs were the most common in the studied population. Given that selective screening of the child population in western Kazakhstan will be carried out for about 2 years (2023–2024, recruitment of high-risk children), the incidence rate for each class of disorders (AAD, OA, FAOD) will be established, taking into account the total number of births each year.

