**FIGURE 1 F1:**
[figure not shown]
Flowchart of the study.

The project timing is calculated for 3 years, 2022–2024. The recruitment of healthy children for establishing reference values started on October 2022, and the overall data collection will last until August 2024 (recruitment of high-risk children began in 2023).

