**FIGURE 2 F2:**
[figure not shown]
Sites for data collection throughout western Kazakhstan.

Children from the western Kazakhstan population with suspected metabolic disorders are examined for congenital metabolic disorders and referred by primary care neonatologists and pediatric consultants between October 2022 and August 2024 based on their clinical symptoms associated with metabolic disorders. The study includes newborns and children being treated in maternity wards and pediatric clinics of 7 pediatric hospitals in the region. Patients with suspected IEM from all sites are referred to the Regional Tertiary Care Center or the Mother and Infant Health Center in Aktobe, or their samples are sent from other involved hospitals. Patient information is obtained from the Individual Registration Cards (IRCs) completed by study participants. The completed questionnaires are checked by the researchers. In case of improper collection, data must be removed from the study if it is impossible to check adequately. The IRC sample and other supplementary materials are placed in the *clinical. trials.gov* Register (https://www.clinicaltrials.gov/study/NCT05910151) and a publicly available repository (https://osf.io/cmrh7/).

To set reference values of 15 AAs, 35 ACs, and SuAc, healthy participants without any disease are included in the study. A total of 750 healthy male and female children aged 1 day to 18 years are recruited based on random selection. Participants will be balanced by gender and place of residence. Considering the distribution of urban and rural populations in western Kazakhstan, approximately half of them will be selected in urban areas, the other half in rural areas. A summary of the age, gender, and geographic distribution of study participants will be presented in Table 1.

**TABLE 1 T1:** Demographic data to be collected on study participants.

Variables	Selective screening (n = 1,500)	Healthy children (n = 750)
Age in days, years (median, range)		
Weight in grams, kilograms (median, range)		
Gender		
Male, n		
Female, n		
Geographic distribution		
Aktobe province		
Atyrau province		
West Kazakhstan province		
Mangystau province		
Urban population		
Rural population		

Screened children with positive first-level LC-MS/MS test results will be referred for second-level screening.

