#### 2.2.4 Criteria for inclusion in the selective screening for IEM

Children from 1 day to 18 years of age will be enrolled for selective screening for IEM if one of the main criteria or two or more additional criteria (symptoms) are identified. The inclusion criteria for IEM selective screening are presented in Table 2.

**TABLE 2 T2:** Criteria for inclusion in the selective screening for IEM.

Main criteria (symptoms)	Sudden deterioration in the clinical condition of the child after a period of normal development (days, weeks, months): Acute metabolic encephalopathy lethargy (coma) seizures resistant to antiepileptic therapy
	Hepatomegaly (hepatosplenomegaly)
	Metabolic acidosis with increased anion gap
	Multiple fractures
	Child mortality in the family from diseases with similar symptoms
Additional criteria (symptoms)	Treatment-resistant seizures
	Abnormal muscle tone: dystonia, hyperkinesis, hypotension
	Speech retardation
	Mental retardation of unknown cause
	Cardiomyopathy
	Tachypnea
	Frequent spitting up (vomiting)
	Osteoarticular anomalies (joint stiffness, chest deformity, rickets-like changes)
	Hernias (umbilical, inguinal-scrotal)
	Persistent or recurrent hypoglycemia
	Metabolic alkalosis
	An increase in ketone bodies in the blood and (or) urine
	Hyperammonemia
	An increase in the level of liver enzymes (ALAT, AST) more than 1.5 times
	Increase in the level of creatine phosphokinase (CPK) by more than 2 times
	Decrease in the level of alkaline phosphatase (AP) below the age norm
	Imaging or electrophysiological examinations indicating a metabolic disorder
	Leukopenia
	Thrombocytopenia
	Abnormal odor of urine, body, earwax, any unusual odor
	Hair growth disorders, alopecia
	Ophthalmic anomalies
	Unusual appearance, dysmorphic features
	History of death of a previous sibling of unknown cause
	Parents’ consanguinity
	Positive family history with metabolic disorders

Exclusion criiteria:

Patients having the following conditions will be excluded:1. Perinatal brain injury,2. Brain injury,3. Infections of the central nervous system,4. Toxicological diseases,5. Tumors,6. Chromosomal abnormalities,7. Symptoms specified in the Inclusion criteria, but with a confirmed diagnosis of any disease other than Amino acid disorders (AAD), Fatty acid oxydation disorders (FAOD), or Organic acidemias (OA).

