Indices of sensitivity (Sn), specificity (Sp), positive predictive values (PPVs), and negative predictive values (PVN) will be calculated for each diagnostic test under consideration. PPVs will be calculated by dividing the total number of true positive cases by the total number of true positive and false positive cases. The detection rate will be calculated by dividing the number of cases diagnosed by the number of screened children with suspected metabolic disorders. Multiple linear regression coefficients will be calculated to assess the relationship of each analyte with the factors of gender, weight, and place of residence. Due to the number of variables subjected to analysis, and the anticipated presence of multiple outcomes, the included tests may not be sufficient. So, the cluster analysis and, possibly, the decision-tree method will be applied. Decision trees break down complex data into more manageable parts, beneficial in prediction analysis, data classification, and regression. A dimensionality reduction method, principal component analysis (PCA), will also be applied. Two-sided levels <0.05 are assumed to be statistically significant. Statistical analysis will be carried out using the statistical packages IBM SPSS v. 23.0 (IBM, Armonk, NY, United States), Statistica (StatSoft, Inc., Tulsa, OK, United States, v. 10), and R 3.3.2 (R Foundation for Statistical Computing, Vienna, Austria.)

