## 4 Discussion

The present study assumes only selective screening for IEM. Implementing ENBS, which allows for thoroughly assessing the prevalence of IEM in the child population of western Kazakhstan, is currently unavailable due to a lack of proper financing. In addition, given that the overall prevalence of IEM in populations is relatively low, less than 1:100,000 for most of them, coverage for expanded newborn screening should be total. Besides, it is known that not all IEMs are diagnosed during ENBS, as some disorders debut at a later age (Hassan et al., 2016). Nonetheless, the data of selective screening conducted among children at high risk of IEM, given the inclusion in the study of the largest pediatric hospitals in western Kazakhstan, can serve as a basis for calculating the relative frequencies of various IEMs in the child population of the region.

Detection rates for selective screening and incidence will be calculated according to the number of children born alive in the region during the study period, in 2023–2024, for each specific disease. These data will allow for estimating the number of affected male and female children and determining which IEMs are the most common. The frequencies of each IEM revealed across the child population of western Kazakhstan will be matched with incidence data in other regions of the world.

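### Incidence relates cases aged 0–18 years to births of 2023–2024 without separating new from long-standing cases, and the detection rate is given two different denominators

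*Protocol article*

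**What the plan says.** **Incidence.** Section 3.4 of the Protocol article states: "Detection rates for selective screening and incidence will be calculated according to the number of children born in western Kazakhstan during the study period", which it gives as 2023–2024, for each specific disease. Section 4 (Discussion) repeats it almost word for word: "Detection rates for selective screening and incidence will be calculated according to the number of children born alive in the region during the study period". For the disorder groups, section 3.4 adds that "the incidence rate for each class of disorders (AAD, OA, FAOD) will be established, taking into account the total number of births each year".

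**Who the cases are.** Section 2.1 calls the design cross-sectional. Section 2.2.4 sets the age range: "Children from 1 day to 18 years of age will be enrolled for selective screening". Its exclusion 7 removes children with a confirmed diagnosis of some other disease. It does not remove children already known to have an amino acid disorder, organic acidemia or fatty acid oxidation disorder.

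**Detection rate.** Section 3.2 gives an explicit formula: "The detection rate will be calculated by dividing the number of cases diagnosed by the number of screened children with suspected metabolic disorders".

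**Window.** Section 2.1: "the overall data collection will last until August 2024 (recruitment of high-risk children began in 2023". Section 2.2.2: children are "referred by primary care neonatologists and pediatric consultants between October 2022 and August 2024". Section 3.4 describes about two years, 2023–2024.

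**The concern.** The numerator, as far as the article describes it, can include any affected child up to age 18. The denominator is the births of two calendar years. A child born in 2012 whose disease has been present for years but is first recognised in this study counts as a case, although that child's birth is outside the denominator. Nothing in sections 3.2, 3.4 or 4 limits cases to newly arising ones or assigns them to birth years.

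The resulting figures have real uses. Task 3 compares the frequency of each disease with published reports, and the hypothesis in section 1 is that frequencies are lower than where consanguineous marriage is customary. Section 4 plans to match the frequencies with incidence elsewhere and says that the future newborn panel will depend in part on them. If long-standing cases are mixed in to a different degree for each disease, both the level and the order of the diseases can mislead.

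The births sentence also names the detection rate, which section 3.2 defines on another denominator, and the case and birth windows do not coincide.

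**Working it through.** The article states no incidence figure, so there is none to reproduce.

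**Inputs (section 2.2.1).** 1,500 children screened; expected frequency 2–2.5%; 69,000–73,000 live births a year in the three years before the project. I assume the birth numbers stay unchanged.

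**1. The planned ratio.** Expected cases: 1,500 × 0.02 = 30 to 1,500 × 0.025 = 37.5. Births in two years: 2 × 69,000 = 138,000 to 2 × 73,000 = 146,000. The ratio is 30/146,000 = 20.5 to 37.5/138,000 = 27.2 per 100,000.

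**2. When this ratio equals birth incidence.** Let *q* be the true birth incidence of cases presenting by age 18, *b* the births per year, and *Y* = 2 years. With constant births and no deaths or migration, new cases at all ages in *Y* years number *q·b·Y*. Divided by *b·Y* births, this is *q*: the ratio to truth is 1.00, whatever the age at presentation.

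**3. What a backlog adds.** Children under 18 who presented before the window number *q·b·*(18 − *m*), where *m* is the mean age at presentation among those presenting by 18. If a share *f* of them is picked up as cases, the ratio to truth is

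R = 1 + *f*·(18 − *m*)/2.

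With an exponential age at presentation truncated at 18 years (assumed; nominal means 0.25, 2 and 5 years give *m* = 0.25, 2.00 and 4.49):

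| Nominal mean age | *f* = 0 | 25% | 50% | 100% |
|---|---|---|---|---|
| 0.25 y | 1.0 | 3.2 | 5.4 | 9.9 |
| 2 y | 1.0 | 3.0 | 5.0 | 9.0 |
| 5 y | 1.0 | 2.7 | 4.4 | 7.8 |

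The values of *f* are assumptions; the article gives nothing from which to estimate them. Some backlog is plausible, because section 1 describes earlier selective programmes as sporadic and uncompleted. An undiagnosed backlog should be small for phenylketonuria, which section 1 places in a national newborn programme begun in 2007, and for disorders fatal early in life. So *f* differs by disease.

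**4. Incomplete capture.** If only a share *c* of new cases is found, R = *c* + *f*·(18 − *m*)/2. With *c* = 50% and *m* = 2, R falls below 1 whenever *f* is under 0.5/8 = 6.25%. Enrolment through seven hospitals, with 1,500 children planned, makes *c* below 1 likely, so R can lie on either side of 1.

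**5. Detection rate.** Per screened child: 30/1,500 = 2% to 37.5/1,500 = 2.5%. Per birth: 0.021–0.027% (step 1). The denominators differ by 138,000/1,500 = 92 to 146,000/1,500 = 97.

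**6. Window.** January 2023 to August 2024 is 20 months, the most that a start in 2023 allows. October 2022 to August 2024 is 23 months. Against 24 months of births, 20/24 = 0.83 and 23/24 = 0.96: a shortfall of about 17% or 4%.

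**The case against.** The strongest objection is that dividing diagnoses in a period by births in the same period is not an error in itself. That stands: step 2 gives a ratio of exactly 1 under its conditions.

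A reader might infer that inflation equals one over the share of cases born in 2023–2024. It does not. With a mean age at presentation of 2 years and no backlog at all, about 37% of new cases are born inside the window. That rule would report about 2.7-fold inflation where there is none.

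A reader might also infer a 9-fold error from 18 birth years over two. That needs essentially the whole backlog to be found. Spreading the same cases over 18 birth years gives 2.3–3.0 per 100,000 (30/(18 × 73,000) to 37.5/(18 × 69,000)), but this is not a true value either.

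On the detection rate, section 3.2 is explicit, Table 5 counts cases among the 1,500, and section 4 cites selective-screening detection rates of 0.29% to 10.8%, a per-child scale. The births sentence can therefore be read as attaching births only to incidence. This makes the conflict one of wording. Since the sentence appears twice and on its plain reading says otherwise, it still needs correcting.

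Incidence is not among the primary outcomes in section 3.1, and a shared births denominator cancels when diseases are ranked. The cancellation does not remove unequal backlog in the case counts. Finally, a rule for assigning cases to birth years may exist in a fuller document. The article nevertheless fixes the denominator and calls the result incidence.

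**Conclusion.** The point holds as a mismatch between numerator and denominator. Followed as written, the plan can mix long-standing cases aged 0–18 into a figure labelled incidence. The possible overstatement runs from none to roughly 9–10-fold, with about 3-fold (2.7–3.2) if a quarter of the backlog is found. It is uneven across diseases, and incomplete capture works against it. The documents do not fix the net direction, so they do not support saying that the frequencies will be inflated, or by how much.

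The detection-rate conflict is separate. It is a 92–97-fold difference between denominators on the plain reading, and it contributes nothing to the backlog range. The window mismatch is smaller, about 4–17% downward.

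These sizes assume constant births of 69,000–73,000 a year, no deaths or migration, an exponential age at presentation, and illustrative backlog shares.

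**What to change.** - **Detection rate.** Keep confirmed cases over screened children, as in section 3.2, and take the detection rate out of the births sentences in sections 3.4 and 4.
- **Birth incidence.** Assign each confirmed case to its birth year. Count cases born in the window over births in the four provinces in the same months. Label it a minimum, and state that follow-up is short and that late-onset disorders are undercounted.
- **All ages.** Report confirmed cases aged 0–18 over the resident population of that age, as a minimum prevalence and not as incidence.
- **Window and precision.** Reconcile sections 2.1, 2.2.2 and 3.4 to one recruitment window for cases and births, and give exact Poisson intervals.

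The cost is wording plus one population figure. Age is already recorded (Table 1), and section 4 plans to report age at symptom onset. The statistical price is fewer cases for birth incidence. If 37% of 30 cases were born in the window (the 2-year illustration, all cases new), about 11 would remain, and the relative standard error would rise from 1/√30 = 18% to 1/√11 = 30%.

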## 2 Methods and analysis

### 2.1 Study design and timing

This observational study, uses a cross-sectional design due to its screening nature. The data for the present research will be derived from a selective LC-MS/MS IEM screening of 1,500 clinical-risk children aged 1 day to 18 years and 750 healthy controls of the same age to set reference values for 15 AAs, 35 ACs, and SuAc. The main points of the research are presented in Figure 1 (Flowchart of the study.)

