### 2.2 Selection of subjects

#### 2.2.1 Sample size estimation

When calculating the sample size for the upcoming project on selective screening, we relied on published similar studies. Researchers pointed out the following essential factors contributing to the sample size calculation: Daniel’s formula for prevalence studies in case of expanded screenings, the reported frequencies of different IEM within the studied populations, and the number of infants born in the country during the period of interest (Yoon et al., 2005; Golbahar et al., 2013; Hassan et al., 2016; Shibata et al., 2018; Sarker et al., 2019; Manta-Vogli et al., 2020). Notably, many researchers corrected their calculations, considering the situation with consanguineous marriages in their country.

According to the review by Shibata N et al., the IEM overall detection frequency was 3.0% (1.2% in Japan and 9.2% in other Asian countries) (Shibata et al., 2018). Yoon et al. reported 5.4% IEM among South Korean annual births (Yoon et al., 2005). Of these data on IEM frequency throughout Asian countries, Mongolian values (1.6%) have attracted our attention due to the similar nomadic history and way of life where consanguineous marriages were strictly forbidden (Shibata et al., 2018). Along with that, the Mongolian index does not include all types of IEM except the most distributed.

Based on mentioned factors, we requested data on the number of childbirths across the four provinces (oblasts) of western Kazakhstan within 3 years before the project started. The average rate of infants born alive annually ranged between 69–73,000 (https://stat.gov.kz/en/industries/social-statistics/demography/publications/). Thus, we have decided to build on the IEM average frequency of 2%–2.5% and determined the expected sample size of 1,500 children for selective screening with 750 healthy controls.

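### The per-birth incidence divides cases aged 1 day to 18 years by the births of 2023–2024 only, so numerator and denominator describe different birth cohorts

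*Protocol article*

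**What the plan says.** Section 3.4 fixes the denominator for each disease: "incidence will be calculated according to the number of children born in western Kazakhstan during the study period", which it gives as 2023–2024. Section 4 (Discussion) repeats it, using the "number of children born alive in the region during the study period, in 2023–2024", and adds that the frequencies will be set against incidence data from elsewhere in the world.

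On the cases, section 3.4 says "The data will include the total number of IEM cases in the high-risk group of children". Section 2.2.4 defines that group: "Children from 1 day to 18 years of age will be enrolled for selective screening for IEM". Section 2.1 says that the study "uses a cross-sectional design due to its screening nature".

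No section restricts the incidence numerator to children born in 2023–2024, assigns a case to its own birth year, or extends the denominator to earlier years. The limitations listed in section 4 do not mention the point.

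**The concern.** A child of nine diagnosed in 2023 counts as a case but was never among the births in the denominator. A rate built this way mixes cases from many birth cohorts and divides them by two. How far it departs from a birth incidence depends on how old the referred children happen to be. That can differ by disease, because age at presentation differs, so the per-disease rates may be distorted unequally.

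The use most exposed is the comparison with other regions in section 4. It bears on the study hypothesis in the Introduction, that frequencies will be lower than where consanguineous marriage is customary. A rate that carries an unreported factor set by the age mix of cases cannot support that comparison.

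**Working it through.** The protocol states no incidence figure, so there is none to reproduce. The check works out what its rule would give under its own planning values.

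**Inputs**
- Screened children: 1,500 (section 2.2.1).
- Expected frequency among them: 2%–2.5% (section 2.2.1).
- Births: "The average rate of infants born alive annually ranged between 69–73,000" (section 2.2.1), assumed to continue through 2023–2024.
- Age of screened children: 1 day to 18 years (section 2.2.4). Recruitment in 2023–2024 therefore reaches back to birth years of about 2004/05, or about 18–20 birth years.
- Share f of cases born in 2023–2024: not given, so varied as an assumption.

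**Rate under the stated rule**
- Cases: 1,500 × 0.02 = 30; 1,500 × 0.025 = 37.5.
- Births in two years: 2 × 69,000 = 138,000; 2 × 73,000 = 146,000.
- Lowest rate: 30 / 146,000 = 20.5 per 100,000, or 1 in 4,867.
- Highest rate: 37.5 / 138,000 = 27.2 per 100,000, or 1 in 3,680.

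**Rate with cases and births from the same cohort**

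Only f × cases belong over these births, so the planned rate divided by the matched rate is 1/f.

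| Assumed f | Cases born in window (of 30; of 37.5) | Matched rate per 100,000 | Planned ÷ matched |
|---|---|---|---|
| 100% | 30; 37.5 | 20.5–27.2 | 1 |
| 80% | 24; 30 | 16.4–21.7 | 1.25 |
| 50% | 15; 18.75 | 10.3–13.6 | 2 |
| 25% | 7.5; 9.4 | 5.1–6.8 | 4 |
| 11% (even spread, 2 of 18 years) | 3.3; 4.2 | 2.3–3.0 | 9 |

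**Does 1/f measure the error against true incidence?** Not by itself. Two limiting cases show why.
- *All cases newly diagnosed, births constant, detection in steady state.* Diagnoses at all ages over two years then equal two years' births times the true birth incidence. The ratio to true incidence is 1.0, whatever the ages at diagnosis.
- *The whole undiagnosed backlog aged 0–17 is found at once.* If onset is spread evenly over 18 years, affected children number (1 + 2 + … + 18)/18 = 9.5 annual cohorts' worth. Divided by two cohorts of births, the ratio is 4.75. With half of onsets in the first year it is 6.75. With onset falling by 30% a year it is 7.85. Finding only 2/9.5 = 21%, 1/(6.75) = 15% or 1/(7.85) = 13% of that backlog would bring the ratio back to 1.

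**Follow-up of the matched cohort.** Section 2.1 ends data collection in August 2024. The oldest child born in the window would then be about 20 months old, so the matched rate misses disorders that present later.

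**The case against.** The strongest reply is that diagnoses in a period over births in that period is a recognised approximation to birth incidence. A nine-year-old newly diagnosed in 2023 stands in for a child born in 2023 who will be diagnosed later. The first limiting case confirms this, but it needs new diagnoses and steady detection, and the protocol secures neither. The Introduction describes earlier tandem mass spectrometry programmes as sporadic and unfinished, so a backlog is plausible. The design is cross-sectional. The seventh exclusion in section 2.2.4 removes confirmed diagnoses outside the three target groups, but not children already confirmed within them.

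A reader might infer that the incidence is overstated several-fold, or at least biased upward. The documents do not support that. They give no age mix of cases, and the Introduction says that these disorders appear mostly in early infancy and childhood, which makes an even spread to 18 years a poor central assumption. The benchmark behind 1/f is itself cut off at about 20 months. The number examined is capped at 1,500, from seven hospitals, and section 4 lists this limited number as a limitation. Unreferred children and deaths before testing lower the rate.

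Three further points stand:
- Per-birth incidence is not a primary or surrogate outcome in section 3.1.
- The detection rate in section 3.2 is taken over screened children and is untouched. Ranking diseases by case count is also untouched, because a shared denominator cancels.
- The all-ages numerator is the natural reading of section 3.4, but that section describes the data to be presented and does not formally define the numerator.

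None of this repairs the mismatch. Under-ascertainment is a separate error of unknown size and cannot be relied on to offset it.

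**Conclusion.** The point holds as a mismatch of cohorts. The rule in sections 3.4 and 4 sets cases from about 18–20 birth years over two years of births, so the result is neither a birth incidence for 2023–2024 nor safely comparable with incidence elsewhere. Against cases born in the window the inflation is 1/f; the factors from 1.25 to about 9 rest entirely on assumed values of f. A factor of 3 or more requires that at most a third of cases be born in 2023–2024. Against true incidence, the net direction is unknown.

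Confidence is high for the mismatch and low for its size and direction. It should be fixed before the rates are compared with other regions. It does not touch the listed primary outcomes.

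**What to change.** In sections 3.4 and 4:

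- Make the detection rate among the screened children, already defined in section 3.2, the main frequency.
- Compute birth incidence only from cases born within the denominator window, and label it a minimum cumulative incidence to the end of case finding.
- Report older cases separately, either by birth year over that year's births or as period prevalence over the region's population aged 0–18. Do not pool them with the birth-cohort rate.

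The cost is a change of wording plus published birth and population counts by year; age is already collected (Table 1). The downside is that few cases enter the birth-cohort rate. At f = 11%, about 3 to 4 of the expected 30 to 37.5 would remain, across 37 disorders. Later-presenting disorders would be under-counted in that rate, which is why it must be called a minimum.
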